#### Recruitment

The population will be informed about the study and the contact details via social media platforms, newspaper, radio, and television advertisements.

#### Flow and timing

A toll-free phone number will be available for all interested in participation. By dialling this number, the participant will be informed about the trial through a pre-recorded voice message, including the study rationale, conditions of participation, the process of the study, and the information on data protection. Willing participants will be redirected to an available operator, who will ascertain eligibility. Following verbal consent and randomisation, the operator will obtain key personal information of the participants and all study-related information (Fig. 1). The allocation will not and cannot be concealed from the operator, but it will be concealed from everyone else (participants, caregivers, outcome assessors).

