### Study population

#### Inclusion and exclusion criteria

The inclusion criteria of our selective primary prevention programme are as follows: (1) age over 60 years (that is, high-risk individuals) and (2) informed consent to participate. The exclusion criteria are as follows: (1) confirmed COVID-19 (active or recovered), (2) hospitalisation at screening for eligibility, and (3) someone was already enrolled in the study from the same community/household (to avoid potential crosstalk between the study arms).

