### Randomisation and blinding

Computer-generated random sequence randomisation (central) will be performed, after giving informed consent. Due to the expected large sample size, we will use simple randomisation. The allocation ratio will be 1:1. No stratification or blocking will be applied.

In the study, participants will be blinded to the knowledge of the details of differences between the interventions. Everyone else (outcome assessors, caregivers, and data analysts) will be blinded regarding the allocation.

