### Strengths and limitations

We aim to apply lifestyle interventions considered to be safe in a broad population of subjects exposed at high risk of a severe course of COVID-19. The expected health benefits of the interventions considerably exceed its potential harms. With this study design, we can evaluate the effectiveness of (1) the offer of lifestyle intervention vs (2) that of the actual uptake of or compliance to the lifestyle intervention. We expect that the moderate intensity of the personalised multicomponent lifestyle intervention will maximise the effectiveness and, at the same time, prevents low adherence. In addition to the expected beneficial effects regarding the infection, other protective changes are likely regarding cardiovascular and malignant morbidity and mortality on the long-term. The interventions are easy to be delivered while being affordable and implementable for the vast majority of the population.

We expect that there will be limitations in this study [30]. We define cross-contamination that participants on different arms deliberately and unknowingly communicate with each other, leading to the loss of the true effect of lifestyle interventions. To minimise the risk of cross-contamination, we decided to include only one subject from communities with multiple potential candidate participants. Although we can evaluate the actual uptake of the lifestyle interventions, its validity is uncertain due to the patient-reported nature of the data. We cannot anticipate the climax of the epidemics so that the infection rate of the target population may deviate from the assumed 10%. To overcome this, we use sample size-readjustment adaptive design, which may settle the problem with the unpredictable dropout rate as well (although this method cannot counteract chronological changes in the dropout rate throughout the evolution of the pandemic). All data on secondary outcomes are provided by participants and other, less reliable indirect data sources. We anticipate that volunteers give a representative sample of the target population, but we cannot exclude that our study population will be somewhat better educated and highly motivated. Despite the thorough training of the operators, inter-operator variability may be present.

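### Personal details are taken only after randomisation, so the one-per-household exclusion rests, before allocation, on the caller's own answer

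*Protocol article*

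**What the plan says.** All references are to the protocol article.

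- **Inclusion and exclusion criteria.** The third exclusion applies if "someone was already enrolled in the study from the same community/household (to avoid potential crosstalk between the study arms".
- **Strengths and limitations.** The purpose is repeated: "To minimise the risk of cross-contamination, we decided to include only one subject from communities with multiple potential candidate participants".
- **Flow and timing.** A caller hears a recorded message, and then: "Willing participants will be redirected to an available operator, who will ascertain eligibility". The next sentence gives the rest of the order: "Following verbal consent and randomisation, the operator will obtain key personal information of the participants and all study-related information". The same section says the operator cannot be kept unaware of the allocation.
- **Randomisation and blinding.** Allocation is central and comes once consent has been given. On the method, the section states: "Due to the expected large sample size, we will use simple randomisation". The two arms are to be of equal expected size (1:1). On restrictions, it adds: "No stratification or blocking will be applied". The household therefore plays no part in how arms are assigned.
- **Data handling.** Data are recorded after verbal consent. This is compatible with the order above and does not say whether any recording comes before the allocation.

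**The concern.** Age, confirmed COVID-19 and current hospitalisation are facts about the caller, which the caller can report. The third exclusion is different in kind, because it is a fact about the trial's own list of participants. A caller may not know, or may not mention, that a spouse or fellow resident has enrolled. Recruitment by mass media to an open toll-free line for everyone over 60 makes calls from both members of an older couple plausible.

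If identifying details enter the system only after allocation, a match can come to light only once the second person has an arm. Two things are then at stake. A household split between arms is the very contamination that the exclusion exists to prevent, and it pulls the comparison towards no difference. The two members of a household are also not independent observations.

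The wording adds a smaller difficulty. The article does not define a community, so an operator or a database has no workable rule for applying that half of the criterion.

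**Working it through.** **1. Order of steps.** Flow and timing gives: eligibility check, verbal consent and randomisation, key personal information. The third exclusion belongs to the first step. The information against which it could be matched belongs, on the literal text, to the last. Before allocation, what remains is the caller's answer.

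**2. Share of pairs split between arms.** With independent 1:1 allocation, P(opposite arms) = 2 × 0.5 × 0.5 = 0.5.

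**3. The plan's own sample size.** Inputs from the sample size section: 20% event rate in infected controls, 50% risk reduction (so 10%), 90% power, two-sided 5% alpha with a Pocock correction for one efficacy interim (nominal 0.0294 for two looks, critical value 2.178), 10% COVID-19 incidence, 20% dropout. With pooled variance under the null and no continuity correction:

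n = [2.178 × √(2 × 0.15 × 0.85) + 1.2816 × √(0.16 + 0.09)]² / 0.10² = 303 infected per arm.

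303 / 0.10 / 0.80 = 3787.5, which rounds up to the stated 3788. The figure reproduces.

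**4. Size of the dilution.** The article gives no rate of same-household pairs. Let f be the share of participants in such pairs (assumed 2% to 20%). Half the pairs are split, so a share f/2 of controls has a partner in the personalised arm. Assume full crosstalk, meaning that each such control gains the whole intervention effect:

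control rate = 0.20 − (f/2) × 0.10.

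Power is taken at 303 infected per arm and alpha 0.0294. For f = 10% the control rate is 0.195, the difference 0.095 and the mean rate 0.1475:

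z = [0.095 × √303 − 2.178 × √(2 × 0.1475 × 0.8525)] / √(0.195 × 0.805 + 0.10 × 0.90) = (1.654 − 1.092) / 0.497 = 1.13, so power is 87.1%.

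The counts use 2 × 3800 = 7600 participants: pairs = f × 7600 / 2, split pairs = half of that.

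| f (assumed) | Pairs | Split pairs | Control rate | Power |
|---|---|---|---|---|
| 0% | 0 | 0 | 0.2000 | 90.0% |
| 2% | 76 | 38 | 0.1990 | 89.5% |
| 5% | 190 | 95 | 0.1975 | 88.6% |
| 10% | 380 | 190 | 0.1950 | 87.1% |
| 20% | 760 | 380 | 0.1900 | 83.5% |

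The calculation ignores correlation within households and assumes that infected participants are in pairs as often as the rest.

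**The case against.** The strongest reply is that eligibility is settled before allocation. The operator can ask each caller whether anyone in the household has already joined, just as age and past infection may be taken on the caller's word. The article does not list what counts as key personal information, and it does not say that nothing identifying is taken earlier. It is also a condensed account: the schedule figure and supplementary files are not shown, and a fuller call procedure may exist.

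Much of this stands. A reader might infer that the exclusion cannot be checked at all before randomisation. The text does not support that, since a question to the caller is a check, though a weak one for a fact about the trial's own list. Three other inferences also go too far:

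- *Operators who know the arm would remove second members selectively.* Nothing says so. Decisions on dropouts lie with the Steering Committee, and the analysis section favours intention-to-treat.
- *People already enrolled would ring again and be randomised twice.* The article does not mention repeat callers.
- *One participant per community would require some 7,600 separate communities.* The pairing with household, and the stated aim of avoiding crosstalk, point to shared living settings.

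What does not fall away is the stated sequence. The article does more than stay silent on a procedure: it places the collection of personal information after randomisation. The supplementary files are described as covering the questioning and the intervention scripts, not the checking of eligibility.

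**Conclusion.** The point holds in a limited form. As written, the order of steps leaves the trial's main safeguard against contamination resting on self-report until the arm has been assigned, so some second household members may be randomised. That half of any such pairs would be split follows directly from simple 1:1 allocation.

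The likely effect is modest. Power falls from 90.0% to 87.1% with 10% of participants in pairs, and to 83.5% with 20%. Full crosstalk is an upper-end assumption, and partial crosstalk would cost less. The pair rates are assumptions without a source in the article. The sample size of 3788 per arm is unaffected.

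The change is still worth making, because it alters a stated sequence at little cost and lets the exclusion be confirmed before it matters.

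**What to change.** Reorder the call in Flow and timing as follows:

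1. Eligibility questions, including whether a member of the household is already enrolled.
2. Verbal consent.
3. Entry of identifiers and address, with a check against all enrolled participants.
4. Release of the allocation by the central system.

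Reword the third exclusion as a shared address (household or residential institution), and use the same wording under Strengths and limitations. State that any pair found after allocation stays in the intention-to-treat analysis as randomised.

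The cost is a revised call script, a duplicate check linked to the central randomisation, and a few minutes spent on callers who prove ineligible. No change to the sample size is needed.

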**Fig. 1 Fig1:**
[figure not shown]
Schedule of enrollment, interventions, and assessments according to the SPIRIT statement. The asterisk indicates that the anticipated finishing date is the end of the pandemic or development of the vaccine, but no more than 1 year from the enrolment of the last participant

### Outcomes

Based on literature data [5, 26], the primary endpoint will be defined as the composite of any of the following in COVID-19 cases (an accredited laboratory should verify positivity), the rate of:
ICU admissionsHospital admissions (longer than 48 h) for the following reasons:
Arrhythmia (causing hemodynamic instability and requiring continuous monitoring and/or cardiac support, as indicated by mean arterial pressure < 65 mmHg, and/or serum lactate > 2 mmol/L)ARDS (severe hypoxaemic respiratory failure indicated by a PaO_2_/FiO_2_ < 300 mmHg according to the Berlin definition) [27]Circulatory shock (the requirement of continuous vasopressor support to maintain mean arterial pressure ≥ 65 mmHg and/or serum lactate ≤ 2 mmol/L)Deaths

Secondary endpoints are the following:
The number of general practitioner visitsThe number of emergency, hospital, and intensive care admissionsThe length of hospitalisation and ICU stayThe number of organ dysfunctions and failures (central nervous system, cardiovascular, respiratory, renal, liver, haematological)The measurable lifestyle changes (including physical and mental health)The costs of care

The primary and secondary outcomes will be assessed upon the conclusion of the trial, at least 1 year after the enrolment of the last participant.

### Randomisation and blinding

Computer-generated random sequence randomisation (central) will be performed, after giving informed consent. Due to the expected large sample size, we will use simple randomisation. The allocation ratio will be 1:1. No stratification or blocking will be applied.

In the study, participants will be blinded to the knowledge of the details of differences between the interventions. Everyone else (outcome assessors, caregivers, and data analysts) will be blinded regarding the allocation.

### Sample size calculation, interim, and final analyses

The primary outcome is estimated to occur in 20% of COVID-19-infected cases (≥ 60 years of age) receiving the standard of care based on Chinese reports [5]. Due to the lack of data, we hypothesised that our intervention would result in a 50% risk reduction. Considering one interim analysis on efficacy (with the Pocock correction), 90% power, 5% alpha (superiority design, two-sided), a dropout rate of 20% [28, 29], and assuming 10% incidence of COVID-19 in the target population, the estimated sample size is 3788 (rounded up to 3800) subject per study arm. The calculation was performed by Stata (version 15, Philadelphia, the USA).

We plan to hold three interim analyses: the first for sample size re-estimation at 5% of the target sample size due to the dropout rate, the second for safety assessment at 10% of the target sample size, and the third for efficacy assessment and sample size reestimation at 50% of the target sample size. Early stopping will be executed if (1) safety concerns arise during the interim analysis; (2) the statistical power reaches at least 90% and *p* < 0.05 at the efficacy interim analysis (stopping for benefit); (3) the statistical power does not reach 10%, *p* > 0.05, and the event number does not reach the assumed 10% for the whole population at the efficacy interim analysis (that is, 380 events for the primary outcome; otherwise, the interim analysis is postponed and repeated when the event number reaches 380 events) (stopping for futility); and (4) the consequences of the pandemic make further recruitment or follow-up impossible (stopping for unfeasibility).

In the final analysis, the intention-to-treat analysis will be favoured over per-protocol (or “as-treated”) analysis. We expect a full dataset for the primary endpoint (since the Hungarian Ministry of Interior will provide these data). If for any reason, data will be missing for the primary outcome, we will use available case analysis. The “last observation carried forward” strategy will be followed to impute missing data for other outcomes measured during the study. Missing more than one consecutive interventions after the initial assessment or withdrawal of consent during follow-up results in the dropout of the patients unless hospitalisation is required in the meantime.

In descriptive statistics, the count and percentage will be provided for each treatment arm for binary outcomes. For continuous outcomes, *n*, mean, median, interquartile (Q3–Q1), standard deviation, minimum, and maximum values will be provided for each treatment arm. In a univariate comparative analysis, we will calculate relative risk with 95% confidence interval (CI) when comparing the primary endpoint between two groups (alpha = 5%) with a reference arm using non-repeated intervention complemented with chi-square or Fisher’s exact test (the same strategy will be followed for binary secondary outcomes). For continuous variables, we will use *t* test assuming unequal variances or the Mann-Whitney test. We will perform univariate (Kaplan-Meier and Cox-regression) and multivariate (Cox-regression) survival analysis for binary outcomes. An adjustment will be carried out at least for age, sex, and education. Mixed effect logistic regression will be conducted to estimate the effect of the multicomponent intervention on the outcomes, where the subject IDs will be used as a random subject. The model will be adjusted for changes in smoking habits, alcohol consumption, physical activity, and dietary habits (or body mass index).

All analyses will be carried out with SPSS version 26 and Stata version 15.

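### The only efficacy look is set at half the sample size, but the design's information is infections and events; if half means enrolled, the look falls far short of half the information

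*Protocol article*

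**What the plan says.** All of the interim rules stand in the protocol article, section Sample size calculation, interim, and final analyses.

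- **Timing.** The third interim, which serves both efficacy and sample size re-estimation, is held "at 50% of the target sample size". The text does not say whether this counts participants enrolled or participants followed up.
- **Basis of the size.** "The primary outcome is estimated to occur in 20% of COVID-19-infected cases", and "we hypothesised that our intervention would result in a 50% risk reduction". The calculation adds 90% power, "5% alpha (superiority design, two-sided"), 20% dropout and 10% incidence of infection, and arrives at 3788 per arm, rounded to 3800.
- **Correction for the look.** "Considering one interim analysis on efficacy (with the Pocock correction").
- **Benefit rule.** Stop if power is at least 90% and p < 0.05 at the efficacy interim. No minimum number of events is given.
- **Futility rule.** This is where the event clause sits. It refers to the assumed 10% for the whole population, equates that with 380 primary-outcome events, and otherwise postpones the interim and repeats it at 380 events.

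Under Outcomes, the primary endpoint is defined only in laboratory-verified COVID-19 cases, and outcomes are assessed "at least 1 year after the enrolment of the last participant". Study duration says that the trial ends with the pandemic or a vaccine, and no later than 1 year after the last enrolment.

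**The concern.** A participant contributes to the primary comparison only once infected. Infections accrue over calendar time, and much of that time lies after recruitment ends. A trigger that counts people can therefore be reached long before half the infections have occurred. The usual two-look Pocock level of 0.0294 assumes a look at half the information.

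What is at stake is mainly the usefulness of the look. The trial pays for it with a larger sample, and a look taken very early has little chance of showing even the large effect assumed. The protocol does contain an event count that might have corrected the timing, so the point depends on whether that count works.

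**Working it through.** **1. Reproduce the stated size.** Inputs from the sample size section: 20% v 10% among the infected, 90% power, one Pocock-corrected look (nominal two-sided 0.0294, z = 2.178), incidence 10%, dropout 20%.

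n = [z(α)·√(2·0.15·0.85) + z(β)·√(0.2·0.8 + 0.1·0.9)]² / 0.10²

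= [2.178·0.505 + 1.282·0.5]² / 0.01 = 303 infected per arm.

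303 / 0.10 / 0.80 = 3787.5, rounded up to 3788. This is the stated figure.

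With 0.05 in place of 0.0294, n = 266 and 266/0.10/0.80 = 3325. The look therefore costs 3788 − 3325 = 463 per arm, or about 14%.

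**2. Planned information.** 2 × 303 = 606 infections. Expected primary events: 303·0.20 + 303·0.10 = 60.6 + 30.3 ≈ 91. Half of the information is about 303 infections or 45 events.

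**3. Information when half are enrolled.** The document gives no accrual period, so this step is an assumption shown over a range: uniform accrual over E months, constant infection risk, F months after the last entry. At half enrolment (time E/2), half the sample has been followed for E/4 months on average. At the end, the whole sample has E/2 + F months on average. Hence

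t = (E/8) / (E/2 + F).

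| E (months) | F (months) | t | Infections (606·t) | Events (91·t) | Power at 0.0294 |
|---|---|---|---|---|---|
| 3 | 12 | 2.8% | 17 | 2.5 | 5% |
| 6 | 12 | 5.0% | 30 | 4.5 | 8% |
| 12 | 12 | 8.3% | 51 | 7.6 | 12% |
| 24 | 12 | 12.5% | 76 | 11.4 | 17% |
| 3 | 6 | 5.0% | 30 | 4.5 | 8% |
| 6 | 6 | 8.3% | 51 | 7.6 | 12% |
| 12 | 6 | 12.5% | 76 | 11.4 | 17% |
| 24 | 6 | 16.7% | 101 | 15.2 | 22% |

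F = 12 follows the Outcomes section. F = 6 allows for an earlier end under Study duration. At t = 50%, power at the look is 60%. Under this model t stays below 25% however long accrual lasts. With so few events these powers, from a normal approximation, are only indicative.

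**4. Type I error.** With 0.0294 at both looks and correlation √t between the two test statistics, the overall error is 5.0% at t = 0.5, and from 5.75% (t = 2.8%) to 5.56% (t = 16.7%) over the range above.

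**5. The 380 figure.** 380 = 10% of 3800, which is the assumed number of infections in one arm. As an infection count it is 380/760 = 50% of those expected in both arms without dropout, or 380/608 = 62.5% after 20% dropout. As primary events it is 380/91 ≈ 4.2 times the expectation for the whole trial. Even without dropout and with 20% in both arms, the full trial would give only 760·0.20 = 152.

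**6. When half the information is reached.** On the same model with F = 12, this is at month 0.75·E + 6: months 8.25, 10.5, 15 and 24 for E = 3, 6, 12 and 24. The first three lie after enrolment closes, and the last lies at closure.

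**The case against.** **The protocol does have an event trigger.** A reader might infer that nothing ties the look to infections or events. That is not so: the 380 clause postpones and repeats the interim analysis, and since there is only one efficacy interim, it could be read as governing that look generally. Read as 380 infections, it would place the look at about 50-63% of the information, close to what Pocock assumes. This stands as a statement of probable intent. It does not rescue the plan, because the text labels the count as primary-outcome events, which makes it unreachable, and because the benefit rule carries no such condition.

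**Half the sample may mean half followed up.** The wording allows this, and information would then be 50%. That the look is tied to enrolment is one reading only.

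**The shortfall is assumed.** This is correct. Accrual is not stated, and constant risk is a strong assumption in a pandemic. An early wave would raise the fraction. A reader might conclude that the look is certain to rest on a handful of events; the document does not establish that.

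**The error rate is not seriously inflated.** A reader might infer a material loss of type I error control from the timing. The excess is below one percentage point, and it is computed for 0.0294 at both looks, whereas the written benefit rule is p < 0.05 with at least 90% power. If that power is taken at the observed effect, stopping needs |z| of about 1.96 + 1.28 = 3.24, and an early look would spend almost no alpha. The gap between p < 0.05 and 0.0294 is a separate matter.

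**Re-estimation is not defeated.** A reader might infer that rates could not be estimated at an early look. Dropout would be observed in about 3800 people (half of 7600), and some 17-101 infections would be available on the model above. Pooled rates could be partly estimated.

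**Boundary details may be in an analysis plan that is not shown.** This is fair for the spending function. The trigger and the 380 figure, however, are fixed in the article itself.

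**Conclusion.** The point holds in limited form. The size is built on about 606 infections and 91 primary events, while the look is scheduled by sample size. If that means enrolled, the look carries about 3-17% of the information under the accrual, risk and follow-up assumptions stated, with a 5-22% chance of crossing 0.0294 under the hypothesised effect. The harm is a look that is unlikely to be useful although 463 participants per arm were added to pay for it. Any loss of error control from the timing is minor. Independently of the accrual assumptions, the 380 figure is wrong as labelled, and the two triggers need to be reconciled.

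**What to change.** - Trigger the efficacy look at about half the planned information, pooled over arms: about 303 confirmed infections or about 45 primary events. Name one of the two as the trigger, since they coincide only if the assumed event rates hold.
- Replace the 380-primary-event figure so that it matches, and state that the count governs the benefit rule as well as the futility rule.
- Set the boundary by a Pocock-type alpha-spending function at the information actually reached.
- Keep sample size re-estimation separate, as a blinded look at pooled infection and dropout rates while enrolment is still open. Moving it to 45 events would, on the model above with 12 months' further follow-up, put it at or after the close of enrolment.

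**Cost.** The calendar date of the efficacy look is not known in advance. It may fall after enrolment closes, in which case an early stop would save follow-up rather than enrolment. The planned sample size need not change.

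### The interim stopping rules use an undefined statistical power in place of the Pocock boundary on which the sample size was built

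*Protocol article*

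**What the plan says.** All of this stands in the protocol article, Methods, under Sample size calculation, interim, and final analyses.

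- **Sizing.** "The primary outcome is estimated to occur in 20% of COVID-19-infected cases" under standard care, and "we hypothesised that our intervention would result in a 50% risk reduction". The design has "90% power, 5% alpha (superiority design, two-sided"), "a dropout rate of 20" per cent, and it is sized "assuming 10% incidence of COVID-19 in the target population". The interim allowance is worded "Considering one interim analysis on efficacy (with the Pocock correction"). The result is 3788 per arm.
- **Timing.** The efficacy interim falls at 50% of the target sample size.
- **Rule (2), benefit.** Stop if "the statistical power reaches at least 90" per cent and p < 0.05.
- **Rule (3), futility.** Stop if "the statistical power does not reach 10" per cent, p > 0.05, and fewer than 380 events have occurred.
- **Rule (1), safety.** Safety concerns are a separate reason to stop.

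The section does not say whether the power is observed or conditional, which effect and which alpha it assumes, or in which direction it counts. The Pocock level appears in none of the rules. The next paragraph gives alpha as 5% for the primary comparison, without a level per look.

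**The concern.** The sample size pays for a Pocock look, yet the decision at that look is handed to a different and undefined quantity. Power computed from the data already in hand is a fixed function of the absolute test statistic, so it adds nothing to the p-value. Pairing it with a p condition gives one threshold in place of two, and that threshold lies far from the Pocock boundary. Because this power ignores the sign of the effect, a futility rule built on it also treats a trend against group B as a reason to continue.

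At stake are the chance of an early benefit stop, what the futility rule does when group B fares worse, and whether two analysts applying the text would reach the same decision.

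**Working it through.** **1. Reproduce the sample size.** Inputs from the sizing paragraph: 20% v 10%, 90% power, 10% incidence, 20% dropout. The Pocock level for two equally spaced looks, two-sided 0.0294 (critical value 2.178), is the standard value and is not printed in the article.

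n = [z_crit √(2 × 0.15 × 0.85) + 1.282 √(0.16 + 0.09)]² / 0.10²

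- At 0.0294: (2.178 × 0.505 + 1.282 × 0.5)² / 0.01 = 303 infected per arm; 303 / 0.10 / 0.80 = 3787.5, so 3788. This is the stated figure.
- At 0.05: (1.96 × 0.505 + 1.282 × 0.5)² / 0.01 = 265.9, so 266; 266 / 0.10 / 0.80 = 3325.

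The Pocock look therefore costs 3788 − 3325 = 463 participants per arm.

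**2. Observed power (plain reading).** Power = Φ(|z| − 1.96) + Φ(−|z| − 1.96).

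| Condition | \|z\| | p |
|---|---|---|
| power 90% | 3.24 | 0.0012 |
| power 50% | 1.96 | 0.05 |
| power 10% | 0.65 | 0.51 |

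On this reading p < 0.05 is redundant in rule (2) and p > 0.05 is redundant in rule (3). With 2.178 in place of 1.96, the limits are p <= 0.0005 for 90% and p > 0.37 for below 10%. If observed power is projected to the final size (z multiplied by √2, critical value 1.96), 90% needs p <= 0.022.

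**3. Chance of a benefit stop.** Binomial outcomes, 151 infected per arm, 20% v 10%, pooled z test:

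- Pocock boundary: 61%.
- Rule (2) with observed power at interim size: 20%.
- Rule (2) with observed power projected to final size: 56%.

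**4. Futility power condition.** Let positive z favour group B. At z = −1, −1.5 and −2 the observed power is 17%, 32% and 52%, so none is below 10%. As an example with 152 infected per arm, 30 events in A against 40 in B gives z = −1.36, p = 0.17 and power 27%: not met. With 30 against 30 the power is 5%: met.

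Chance that the power condition is met, with 20% events in A and 151 infected per arm:

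| Rate in B | Observed power < 10% | Conditional power for B < 10% (design effect, Pocock final limit) |
|---|---|---|
| 20% | 48% | 26% |
| 25% | 29% | 66% |
| 30% | 8% | 92% |

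**5. Conditional power at half information** (c = final critical value).

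- Current trend: Φ[(√2 z − c) / √0.5]. It reaches 90% at z = 2.03 (p = 0.043) for c = 1.96, and at z = 2.18 (p = 0.029) for c = 2.178. The p < 0.05 condition is still redundant.
- Design effect, drift θ = 2.178 + 1.282 = 3.46: Φ[(√0.5 z + 0.5θ − c) / √0.5]. It reaches 90% at z = 1.61 (p = 0.108) for c = 1.96, and at z = 1.92 (p = 0.055) for c = 2.178. Here p < 0.05 is the stricter condition and decides.
- On either form, z = −1 gives conditional power below 10%. With the design effect it is Φ[(−0.707 + 1.73 − 2.178) / 0.707] = Φ(−1.63), about 5%. A harm trend of that size would meet the power condition of rule (3).

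**6. Type I error, two looks, two-sided.**

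| Interim limit | Final 0.05 | Final 0.0294 |
|---|---|---|
| p < 0.05 | 0.083 | 0.067 |
| p < 0.0294 | – | 0.050 |
| p <= 0.0012 (observed power) | 0.050 | 0.030 |

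**The case against.** The article never says that observed power is meant, and a fuller document may define it. A reader might infer that p < 0.05 can never decide a benefit stop, or that the futility rule lets a harm trend run on whatever is meant. The documents support neither. Under conditional power with the design effect p < 0.05 does decide, and under either form of conditional power checked a trend such as z = −1 meets the futility power condition. Nor is harm left unguarded on the observed-power reading: rule (1) stops for safety concerns, and the Safety section has a board review visits to health facilities.

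A strict interim limit is also a legitimate choice. A threshold near p = 0.001 does not inflate error, and on the observed-power reading the power clause is what holds type I error down. That stands, and it limits how the rule may be repaired. It does not explain why the trial was enlarged for a boundary that the rules then leave out.

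The 380-event condition does not rescue rule (3). Read as primary events, it lies far above what the plan itself expects for the whole trial: 2 × 3800 × 0.10 × 0.15 = 114, or about 91 after 20% dropout. The requirement of fewer than 380 would nearly always be satisfied. If 380 means infected cases, the look could fall at 190 per arm, and the benefit-stop chances become 72% v 30% instead of 61% v 20%. The gap remains.

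Design power at half the sample is no alternative reading. At 152 infected per arm it is 60 to 69%, so it could trigger neither rule.

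**Conclusion.** The point holds in this form: both rules hinge on an interim power that the article does not define, and they do not use the Pocock boundary behind the 3788. On the plain reading the benefit rule is p <= 0.0012, with about a 20% chance of stopping under the design effect against 61% at the Pocock boundary. On the same reading the futility power condition is met with probability 48%, 29% and 8% as group B's event rate rises from 20% to 25% to 30%. If conditional power was meant, the effective benefit limit is p of about 0.03 to 0.05, depending on the assumed effect and the final limit, and the futility criticism falls away. A limit that moves from 0.0012 to 0.05 with an unstated definition is itself the defect.

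The figures assume 151 infected per arm at the look, an information fraction of one half, 20% events in group A and a pooled z test. The level 0.0294 presumes two equally spaced looks; a postponed look or a re-estimated sample size would need it recomputed.

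**What to change.** **Rule (2).** Replace the power clause and p < 0.05 together by: two-sided p < 0.0294 (Pocock), in favour of group B. State 0.0294 for the final analysis as well. Do not merely delete the power clause: p < 0.05 alone at the interim gives an overall type I error of 0.083 with 0.05 at the end, or 0.067 with 0.0294.

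**Rule (3).** Replace the power clause and p > 0.05 by: conditional power in favour of group B, under the design effect (20% v 10%) and the Pocock final limit, is below 10%. Mark the rule as non-binding.

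**Cost.** Two rules are reworded and the final level is stated; no extra participants or data are needed. Under the design effect the new futility criterion would be met in about 0.1% of trials, so the loss of power is under 0.1 percentage point. The downside is that a benefit stop at half information becomes more likely, which leaves fewer data for the secondary endpoints.
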